### Sample size

A power analysis was conducted to determine the appropriate sample size. To do so, we used the G*Power software (Version 3.1.9.7) [32]. To detect differences in each group with repeated measures within-between factors (ANOVA) that correspond to a small effect size (0.18), with an alpha risk of 0.05, and a power of 80%, the adequate sample size required for this study in each group will be 64 participants. Assuming an attrition rate of 25% over the course of the three and a half months of the study, we estimate that a total sample of 160 users of a CRS will be required.

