**Methods/design:**

This is a 12-week follow-up multi-centre non-randomized controlled trial design. At least 160 users will be recruited from 13 Community Rehabilitation Services (CRS) in Catalonia. Eligible participants are adult (≥ 18 years old) users of a CRS, who sign a written consent to participate. The experimental group participates in a recovery workshop, in which people learn to develop and implement their own plan of personal recovery, which includes a Wellness Toolbox, a Maintenance Toolkit, a Personal Growth Plan, a Mirror of Relapses, a Crisis Plan, and a Learning Agenda. The control group participates in the usual activities of the CRS. Data is collected using a questionnaire of sociodemographic characteristics, personal recovery, empowerment, hope and perceived social support. The users’ measurements are taken at the baseline and one week after the end of the workshop. The primary outcome measures include the Self-Identified Stage of Recovery and the Maryland Assessment of Recovery in Serious Mental Illness Scale (short version). The secondary outcome measures include the Netherlands Empowerment List, Dispositional Hope Scale, and Multidimensional Scale of Perceived Social Support. Descriptive statistics for characterizing the sample size will be performed. Multivariate analyses for repeated measures designs will be used to evaluate the primary and secondary outcomes. Between-group and within-subject comparisons will be conducted.

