The study protocol has two limitations that should be pointed out. Firstly, we have chosen a non-randomized trial design to do the study. Therefore, outcome evaluation could not be double-blinded. The main reason is that we wanted to include small cities in the sample as well. These populations have a smaller CRS, with fewer places offered and few users. Taking into account the fact that participation in the activities of the CRS is voluntary, there might be not enough people interested in participating in a 12-week training workshop to create a randomized control group. A pre-recruitment consultation revealed that this was the case for at least 3 CRS. Therefore, there is an evident bias, as the people in the experimental group are those interested in participating in a workshop aimed at promoting personal recovery, and the people in the control group are those not interested in this activity.

Secondly, the loss of subjects over the course of the 12-week implementation of the recovery workshop may cause a possible decrease in the statistical power and a selection bias. As this is a training workshop, offered as a voluntary activity, being implemented for the first time at the CRS, of which people had no prior references with respect to what it would be like to participate, it is expected that there will be a higher rate of abandonment of the activity than the average for the usual activities of the CRS. We expect an abandonment rate of around 20-25%. The possible bias risk here is that the people who complete the workshop and the evaluation are those who are most interested in or identify more with what the training offers them.

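### The recruitment target of 160 does not leave 64 completers per group at the protocol's own 25% attrition; it leaves 60, and covers losses only up to 20%

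*Protocol article*

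**What the plan says.** The protocol article, Method, Sample size, gives the whole chain in one paragraph. The calculation was done in G*Power for this purpose: "To detect differences in each group with repeated measures within-between factors (ANOVA"), with differences "that correspond to a small effect size (0.18"), and "with an alpha risk of 0.05, and a power of 80" per cent. The result is that "the adequate sample size required for this study in each group will be 64 participants". The next sentence makes the allowance for loss, "Assuming an attrition rate of 25% over the course of the three and a half months of the study", and concludes that "we estimate that a total sample of 160 users of a CRS will be required".

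The Abstract (Methods/design) repeats the target as a minimum: "At least 160 users will be recruited from 13 Community Rehabilitation Services (CRS) in Catalonia".

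The limitations part of the Discussion returns to dropout with a range: "We expect an abandonment rate of around 20-25" per cent. It names reduced statistical power as one possible result.

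**The concern.** An attrition allowance is meant to ensure that the required number is still there after the losses. Here the required number, the loss rate and the recruitment total are all printed, and the total is too small for the other two. Nothing has been lost through condensation into an article, because every input and the result are on the page.

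What is at stake is the stated justification for the trial's size. A study that recruited exactly its target and lost exactly the share it planned for would finish below the number it says it needs. The Discussion treats dropout as one of the study's two limitations, so this allowance is the planned protection against a risk that the authors themselves stress.

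**Working it through.** **Inputs**
- Required completers: 64 per group, so 2 × 64 = 128 (Sample size).
- Attrition: 25% (Sample size); 20 to 25% (Discussion).
- Recruitment target: 160 (Sample size); at least 160 (Abstract).
- Test: repeated-measures ANOVA, within-between, two groups, effect size 0.18, alpha 0.05, power 80% (Sample size). I read 0.18 as Cohen's f.
- Measurements: two, at baseline and one week after the workshop (Abstract).
- Allocation: the ratio is not stated. I assume equal groups, since a single per-group figure is given.
- Pre-post correlation ρ: not stated. I assume a range of 0 to 0.5.

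**Reproducing the stated total**
- 128 × 1.25 = 160, an exact match.
- 128 / (1 − 0.20) = 160, also an exact match, but at 20% attrition and not the stated 25%.

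The article prints no formula. The first match suggests that the allowance was applied by multiplying up, but does not prove it. The shortfall below is the same however 160 was reached.

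**What 160 delivers**
- At 25% loss: 160 × 0.75 = 120, or 60 per group. The shortfall is 128 − 120 = 8, and 8/128 = 6.25%.
- At 20% loss: 160 × 0.80 = 128, or 64 per group.
- Largest loss that 160 can absorb: 1 − 128/160 = 20%.

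**What 25% attrition requires**
- In total: 128/0.75 = 170.7, so 171.
- With equal groups: 64/0.75 = 85.3, so 86 per group and 172 in total.
- This is 11 or 12 more than 160.

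**What it means for power under the stated test**

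The primary hypothesis is that the workshop group improves more than the control group, so the relevant term is the group-by-time interaction. The G*Power noncentrality for it is λ = f² × N × m / (1 − ρ), with m = 2 measurements, N the total over both groups, and 1 and N − 2 degrees of freedom. With f² = 0.18² = 0.0324:

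| Assumed ρ | λ at N = 120 | Power, N = 120 | Power, N = 128 | Total N for 80% power |
|---|---|---|---|---|
| 0 | 7.78 | 0.79 | 0.82 | 124 |
| 0.3 | 11.11 | 0.91 | 0.93 | 88 |
| 0.5 | 15.55 | 0.97 | 0.98 | 64 |

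The last row bears on the base figure itself. At ρ = 0.5, λ = 0.0324 × 64 × 2 / 0.5 = 8.29 for N = 64, and power is 0.81. On that assumption 64 is the total over both groups and not the number in each. At ρ = 0 the total is 124, or 62 per group, which is close to 64 per group but not equal to it.

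**The case against.** **The Discussion's range covers it.** The Discussion expects 20 to 25%, and at 20% the target of 160 gives exactly 64 per group. That is true, but it holds only at the most favourable end of the range. The Sample size section, where the figure is derived, assumes 25%.

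**The Abstract sets a floor.** It asks for at least 160, and 13 services with up to 10 participants per group allow 13 × 10 = 130 per group, so 172 was within capacity. This limits the practical effect. It does not make 160 the right minimum for a 25% loss.

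**Power may be ample anyway.** This objection stands. A reader might infer from the shortfall that the trial falls below 80% power. A two-sample t-test at 0.50 SD would even supply figures for this: 80.1% with 64 per group and 77.5% with 60. The protocol contains neither that test nor that effect, so those figures do not describe its calculation. Under the stated test, power with 120 completers is below 80% only when baseline and follow-up scores are close to uncorrelated, and then by about one point.

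**The cause is not established.** This also stands. Multiplying by 1.25 reproduces 160 exactly, but so does dividing by 0.80. A reader should not take the wrong multiplication as documented fact.

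**The error is small and late.** The shortfall is 4 per group. The section Eligibility criteria and recruitment describes recruitment in the past tense, January to October 2022. A higher target is probably of no use now, and what remains is a correction to the text.

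**Conclusion.** The stated figures are inconsistent and the total is wrong as written. With 64 per group required and 25% attrition, 160 recruits leave 120 completers where 128 are needed, and the matching target is 171 (172 for equal groups). The completer total and the 171 follow from the protocol's own numbers alone. The split into 60 per group, and the 172, also assume equal allocation.

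The finding goes no further than that. The target does not deliver the evaluable number that the protocol says it needs, but the documents do not support a claim that real power is under 80%. That depends on a pre-post correlation which the article does not give, and for assumed values of 0 to 0.5 the power with 120 completers runs from about 0.79 to 0.97. Those values also rest on reading 0.18 as Cohen's f and make no allowance for similarity of participants within a service.

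The base figure of 64 per group needs confirming too, because at a correlation of 0.5 the stated test needs 64 in total.

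**What to change.** Restate the last part of the Sample size section and bring the Abstract into line, in one of two ways:

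- *The total of 160 allows for 20% attrition and leaves 64 evaluable participants per group*; or
- *With 25% attrition, 160 recruits leave 120 evaluable participants (60 per group)*, followed by the power recomputed for the within-between interaction at a stated pre-post correlation.

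Under the first option, note that the Discussion's expected loss reaches 25%, so that the two sections agree.

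In the same edit, check the G*Power output and state whether 64 is per group or the total, together with the correlation that was entered. If it proves to be the total, the attrition arithmetic should be redone from that figure.

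The cost is a sentence or two in the Sample size section and a matching change in the Abstract. No further recruitment and no design change are needed. The only downside is that the stated attrition margin or evaluable number looks slightly less favourable.

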### Intervention

The recovery workshop of the *Activa’t per la Salut Mental* programme presents and trains how to use a series of materials that facilitate self-determination in developing one’s own recovery plan. These materials include:

Manual for Recovery and Self-Management of Well-Being: This introduces the concept of personal recovery and provides information, guidance and a variety of strategies that individuals can use to develop their own recovery plan [20]. It organizes these resources and strategies based on whether they can be found in ourselves, in our immediate environment (relatives, friends, etc.), in the community, in the professional care network, or in mutual support environments. It offers links to web portals that help them find these resources in the region where they live (e.g., it allows access to the entire network of mutual aid groups in Catalonia).
Personal workbook: This is a practical document that facilitates the organization and management of the strategies and resources that people have at their disposal to develop their own personalized recovery plan [21]. This material organizes the resources according to what they are used for: promoting well-being, having a life project, trying to avoid relapses, identifying the beginnings of a relapse, making advanced decisions to deal with mental health crises more easily, and learning from one’s own experience. In addition, the workbook offers sections to be filled in order to write down their own recovery plan.

The workshop is organized into 12 sessions, each 90 min long, which include conceptual content, participatory dynamics, and periods for collective reflection. Additionally, from the fourth session onwards, an initial quarter of an hour is dedicated to accompanying and/or sharing in groups the advances made by the workshop participants in the development of their personal recovery plan.

Among other specific contents, the participants of the Recovery Workshop learn: (a) the meaning of recovery from the recovery model perspective (i.e., their distinguishing characteristics, origin and principles) and the role of self-determination and self-management in recovery processes in mental health; (b) the importance of having a personalized recovery plan centred on the person and by the person, according to their own preferences and values, identifying their current needs and their own recovery goals, and the need to identify the resources people have within their reach to carry out their recovery process, including professional care resources, but also those they can find in themselves, in their immediate environment, in the community, and in mutual support spaces; (c) the value of well-being for mental health and the importance of including in the daily routine or in daily actions some activities that generate well-being (using the Wellness Toolbox section); (d) the necessity of agency in preventing mental health crises and the importance of identifying what should and should not be done in their own everyday lives to try to reduce the chances of having a relapse (using the Maintenance Toolkit section); (e) how to build or identify one’s own motivations and goals in life, and the importance of having a life project, something to live for (using the Personal Growth Plan section); (f) how to identify the first signs of a relapse (with or without the help of others) and the resources that each person may have available to respond to them (using the Mirror of Relapses section); (g) the importance of identifying who the support people are that one could count on in case of need, whether they are people from the family environment, friends, professionals or mutual support environments (using the Mirror of Relapses and Crisis Plan sections); (h) the need to prepare for possible future relapses or mental health crises, making an own advanced decisions plan (using the Crisis Plan section); (i) how to record and systematize one’s own experience to use it as a source of basic learning to guide their own recovery process (using the Learning Agenda section).

Moreover, a distinctive feature of the Workshop is that not only is it a space for learning and reflection in relation to these contents, but also that it has a practical orientation. People who complete the recovery workshop are expected to have developed their own Recovery and Self-Management of Well-Being Plan, progressing through and completing their Personal Workbook in collaboration with their environment and professional care resources.

The learning objectives and specific content of each session can be found in the Guide for Implementing the Workshops with the Manual for Recovery and Self-Management of Well-Being [22].

The recovery workshop is implemented by CRS professionals, who have previously participated in 20.5 h of training on: (a) the principles of recovery-oriented care; (b) the materials from the *Activa’t per la Salut Mental* recovery workshop; (c) the contents and activities of the Recovery Workshop; and (d) the design of the evaluation of the effectiveness of the recovery workshop study. Additionally, in sessions fifth and tenth of the workshop, experts with experience in the recovery process (users and survivors) participate as trainers. In the fifth session, they share a life story of recovery and, in the tenth session, they explain what participating in a space of mutual support has given them in terms of their recovery process. They also present the network of mutual support that the participants have within their reach.

For their part, the members of the control group participate in the usual CRS activities. These activities include development of cognitive, communication and emotional skills workshops; leisure and free times activities; strengthening of social relationships; training and guidance for job placement; etc. For the most part, these activities take place on a weekly basis or more frequently.

### Outcomes and participant timeline

The primary outcome of the study is personal recovery. The recovery stage will be measured in accordance with Retta Andresen’s proposal [33, 34], and the level of recovery will be measured in line with the proposal of Drapalski and Medoff [35, 36]. Two psychometric instruments are used to measure personal recovery:

#### Self-Identified Stage of Recovery (SISR)

This scale is based on the stages model of recovery, which identifies five stages in the recovery process: moratorium, awareness, preparation, rebuilding and growth [33]. This instrument is a two-part scale. The first (SISR-A) allows the stage of recovery to be assessed, and the second (SISR-B) measures four component processes of recovery (SISR-B). The SISR-A is a single-item, forced-choice measure, with five answer options (from A to E), each presenting one of the stages of the recovery process. The participants have to choose one of these items, identifying at which stage they consider that they currently are. The SISR-B is a 4-item scale, assessing four key component processes of recovery: finding hope, re-establishment of identity, finding meaning and taking responsibility. It uses a Likert scale with six response options, ranging from 1 (Disagree strongly), to 6 (Agree strongly). The total score is obtained from the sum of all the answers, ranging from 4 to 24. A higher score on the scale is indicative of a higher level of recovery.

#### Maryland Assessment of Recovery in Serious Mental Illness Scale – Short (MARS12)

The scale is designed to assess six of the central components of personal recovery, according to the Substance Abuse and Mental Health Services Administration (SAMHSA) definition [37], excluding the components that do not focus on the person but on the service system or community, and combining empowerment and self-direction. These six domains are: self-direction/empowerment, holistic, non-linear, strengths-based, responsibility, and hope. The original instrument is a 25-item scale [35, 36]. For this study, we use the short version, a 12-item scale (MARS12) developed by Deborah Medoff (2015) [38]. MARS12 uses an ordinal Likert scale with five response options, ranging from 1 (Not at all), to 5 (Very much). The total score is obtained from the sum of all the answers, ranging from 12 to 60. A higher score on the scale is indicative of a higher level of recovery.

The secondary outcomes of the study are empowerment, hope and perceived social support. Three psychometric instruments are used to measure these variables:

#### Netherlands Empowerment List (NEL)

This is designed to assess both personal and social dimensions of empowerment. The NEL is a 40-items scale that includes six subscales: (a) Confidence and purpose (12 items); (b) Social support (7 items); (c) Connectedness (6 items); (d) Self-management (5 items); (e) Caring community (6 items); and (f) Professional help (4 items) [39]. This instrument uses a Likert scale with five response options, ranging from 1 (Strongly disagree), to 5 (Strongly agree). The total score is obtained from the sum of all the answers, ranging from 40 to 200. A higher score on the scale is indicative of a higher level of empowerment.

#### Dispositional Hope Scale (DHS)

This is based on the two-factor model of hope, which includes pathways and agency [40]. The DHS is a 12-item scale, of which four are pathways items, four measure agency, and the remaining four are filler items. This instrument uses a Likert scale with four response options, ranging from 1 (Definitely false), to 4 (Definitely true). The total score is obtained from the sum of all the answers, ranging from 12 to 48. A higher score on the scale is indicative of a higher level of hope.

#### Multidimensional Scale of Perceived Social Support (MSPSS)

This scale is designed to assess perceived social support from three sources: family, friends, and a significant others [41]. MSPSS is a 12-item scale, with four items measuring each of the three sources of social support. This instrument uses a Likert scale with seven response options, ranging from 1 (Very strongly disagree) to 7 (Very strongly agree). The total score is obtained from the sum of all the answers, ranging from 12 to 84. A higher score on the scale is indicative of a higher level of perceived social support.

#### Sociodemographic characteristics

Sociodemographic characteristics are collected at the baseline of the study, and they include: age, gender, marital status, education level, working status, diagnostics, and coexistence unit.

(See Additional file 2 for the test battery)

Pre-intervention data collection is conducted around one week before the beginning of the recovery workshop at each CRS. Post-intervention data collection is conducted around one week after the end of the recovery workshop at each CRS.

SPIRIT Fig. 1 shows a summary of all the steps described above.

**Fig. 1 Fig1:**
[figure not shown]
Schedule of enrolment, interventions, and assessment

### Data storage and security

The members of the research team will be responsible for the treatment and custody of the data. The data will be collected using the Qualtrics digital platform, which has a data handling security certificate (DIN EN ISO/IEC 27001:2017). When the data collection is completed, the data will be downloaded to an institutional computer of the University of Barcelona belonging to one of the researchers and then immediately removed from the Qualtrics platform. The data files, to which access will be limited exclusively to the members of the team, will be stored and safeguarded on the institutional cloud (OneDrive UB).

The research team commit to comply with Regulation 2016/679 of the European Union, of 27 April, on the protection of natural persons with regard to the processing of personal data and on the free movement of such data, and the Spanish Organic Law 3/2018, of 5 December, on the protection of personal data and guarantee of digital rights.

### Statistical analysis

To evaluate the effectiveness of the *Activa’t per la Salut Mental* recovery workshop, descriptive statistics for characterizing the sample size will be performed. Multivariate analyses for repeated measure designs will be used for measures of personal recovery, empowerment, hope and perceived social support. Between-group and within-subject comparisons will be performed. In addition, ANOVA and ANCOVA will be used when comparing groups.

Statistical analyses will be performed using JASP software (Version 0.16.3) [42].

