### Study setting and CRS enrolment

The study is conducted in 13 mental health Community Rehabilitation Services (CRS), spread over 75% of the territory of Catalonia. Both large cities (such as Barcelona, with more than 1.6 million inhabitants) and small municipalities (such as Amposta, with just 20,000 inhabitants) have been included. A CRS is a free, public mental health care resource with the aim of comprehensively accompanying people throughout their own recovery process. They offer specialized care designed to promote functional recovery, strengthen psychosocial skills and facilitate people’s inclusion in the community.

The CRS enrolment was conducted eight months before users’ recruitment. Mental health service providers in Catalonia that had previously collaborated with the *Activa’t per la Salut Mental* programme were invited to participate. Together, these 13 CRS offer community mental health services to a region with a total population of 1,700,000 people.

Prior to the study, from 16 April to 5 October 2021, at least two professionals from each CRS received 20.5 h of training on: (a) what personal recovery is and how to promote it; (b) how to draft their own personal recovery plan (with the new materials created in Catalonia) [20, 21]; (c) how to implement the recovery workshop of the *Activa’t per la Salut Mental* programme [22]; and (d) how to evaluate this recovery workshop (including instruments and study design).

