### Eligibility criteria and recruitment

Eligible participants are adults who take part in the activities of a CRS, and who consent to participate in the study. There are 15 potentially eligible CRS whose professionals had previously attended the recovery workshop training course for trainers. Of these, only the CRS that have agreed to participate in the research, allow accessibility, and commit to the continuity of the project have been or will be involved in this study.

The inclusion criteria for participants are: (a) aged over 18 years and under 65 years; (b) user of a CRS; and (c) signature of the informed consent and commitment to participate. The exclusion criteria are: (a) presence of relevant cognitive impairment and comprehension difficulties; and (b) presence of severe or decompensated somatic disease.

The CRS professionals oversee the recruitment, offering all users of the service meeting the inclusion criteria the option of participating in an evaluated recovery workshop as part of the range of activities offered by the service. All users interested in participating can sign up, up to the maximum capacity of 10 participants. If the maximum capacity of workshop participants is exceeded, the last people signed up will remain on a waiting list for future cycles of the workshop. This is the standard procedure for all regular CRS activities. For the control group, the CRS professionals will follow the same procedure. If there are more than 10 people interested in participating in the control group, the CRS professionals will carry out intentional sampling, taking into account the demographic variables (age, sex, level of education, etc.) of the experimental group, to form a relatively equivalent group with respect to these variables.

All users interested in participating in the study are invited to a session prior to the start of the workshop, in which the research team resolves any possible doubts about the study’s aim and procedures. Their written informed consent is also obtained in this session.

CRS professionals assign an alphanumeric code to all trial participants, both in the experimental group and in the control group. The members of the research team do not have access to the information related to the group to which the participants belong until the interpretation phase of the collected and processed data.

The recruitment period ran from January to October 2022.

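### The workshop is delivered in groups at 13 centres, but neither the sample size nor the named analyses allow for correlation among members of the same workshop.

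*Protocol article*

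**What the plan says.** Study setting and CRS enrolment names 13 community rehabilitation services (CRS), each with at least two trained professionals. Eligibility and recruitment fixes the size of a workshop: "All users interested in participating can sign up, up to the maximum capacity of 10 participants". The CRS professionals also form the control group. The Intervention section describes 12 sessions of 90 minutes with collective reflection and, from the fourth session, time to support or share in groups each participant's progress. The CRS's own professionals lead it. Controls take the usual mix of CRS activities.

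The Sample size section uses one individual-level calculation, "To detect differences in each group with repeated measures within-between factors (ANOVA"), with effect size 0.18, alpha 0.05 and power 80%. It concludes that "the adequate sample size required for this study in each group will be 64 participants". The only inflation is for attrition: "Assuming an attrition rate of 25% over the course of the three and a half months of the study", giving 160 in total.

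For the analysis, "Multivariate analyses for repeated measure designs will be used for measures of personal recovery, empowerment, hope and perceived social support", with ANOVA and ANCOVA for comparing groups. No ICC, design effect, centre factor, workshop factor or cluster-robust variance appears. The Discussion lists two limitations, the non-randomised design and attrition. Clustering is not one of them.

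**The concern.** People who attend the same 12 sessions share facilitators, peers and discussion, so their outcomes are likely to be correlated. An ANOVA on individuals counts them as independent. A good or poor facilitator at a few services would then look like evidence for or against the programme, and the test of the primary hypothesis would not hold its 5% level.

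There is also a centre level. Where a CRS supplies both arms, its general effect is common to both and mostly drops out of the comparison. Leaving it out of the model keeps that variation in the error term and can make the standard error too large. The two omissions act in opposite directions, and the documents do not show which dominates. The result is meant to inform whether the workshop enters the regional service portfolio, so the stated precision matters.

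**Working it through.** **Inputs from the article.** Effect size 0.18 (read as Cohen's f), alpha 0.05, power 0.80, 64 per group (128 evaluable), 160 enrolled, 13 CRS, at most 10 per workshop, two measurements.

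**Assumptions.** ICC 0.01, 0.05 or 0.10, for the quantity tested (change or baseline-adjusted score). One workshop per CRS, equally filled: 160/2 = 80 and 80/13 = 6.15 enrolled per workshop. The stated maximum of 10 is the upper case. Clustering is in the workshop arm only, since no control therapy group is described. The correlation between measurements, ρ, is not stated, so 0 and 0.5 are both shown.

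**Step 1, the article's own figure.** For the group-by-time test with 2 groups and 2 measurements, λ = f²·N·2/(1−ρ), on 1 and N−2 degrees of freedom.
- ρ = 0, N = 128: λ = 0.0324 × 128 × 2 = 8.29, power 0.815. A total of 124 (62 per group) reaches 80%.
- ρ = 0.5, N = 128: λ = 16.59, power 0.981. Here a total of 64 already gives 0.809.

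So 64 per group is approached only with ρ near 0. Neither version has a clustering term.

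**Step 2, design effect.** In the workshop arm DE = 1 + (m−1)·ICC. With equal arms the variance of the difference is multiplied by D = (1+DE)/2. The actual level of a nominal 5% test is 2·[1−Φ(1.96/√D)]. Power uses λ/D.

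| m per workshop | ICC | DE | D | Actual level | Power, ρ = 0 | Power, ρ = 0.5 |
|---|---|---|---|---|---|---|
| 6.15 | 0.01 | 1.052 | 1.026 | 5.3% | 0.806 | 0.979 |
| 6.15 | 0.05 | 1.258 | 1.129 | 6.5% | 0.767 | 0.967 |
| 6.15 | 0.10 | 1.515 | 1.258 | 8.1% | 0.722 | 0.950 |
| 10 | 0.01 | 1.090 | 1.045 | 5.5% | 0.798 | 0.977 |
| 10 | 0.05 | 1.450 | 1.225 | 7.7% | 0.733 | 0.955 |
| 10 | 0.10 | 1.900 | 1.450 | 10.4% | 0.660 | 0.919 |

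**Step 3, simulation check on the level.** Null trials were analysed with a t-test that ignores workshops. With 13 workshops of 6 the level is about 5.2%, 6.4% and 7.5% to 7.9% at ICC 0.01, 0.05 and 0.10. With 8 workshops of 10 it is about 10.3% to 10.7% at ICC 0.10. These agree with the formula to within simulation error and its normal approximation.

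**Step 4, sensitivity.** The power columns pair 128 evaluable people with the enrolled workshop size. With evaluable people only, 64/13 = 4.92 per workshop, and power at ρ = 0 is 0.779 and 0.743 at ICC 0.05 and 0.10, with a level of 6.1% and 7.3%. In the other direction, about 13 workshops leave fewer degrees of freedom than N−2, so an adjusted test has slightly less power than shown.

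**The case against.** The strongest reply is that the analysis section is a short article summary. It lists no covariates or factors at all, and an ANCOVA could carry CRS as a factor. Model terms are often left to the full plan. This has weight for the centre term. It does not remove the point. The power calculation is complete in the article and assumes independence. A CRS factor alone would absorb shared centre effects but not the extra correlation within a workshop. The methods followed as named leave that correlation out.

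Three stronger readings are tempting and are not supported.
- A reader might infer that the trial is underpowered. On the article's own test this depends on ρ: at 0.5, power stays at about 0.92 or more even with workshops of 10 and ICC 0.10.
- A reader might infer that the false-positive rate doubles in general. With workshops of about 6, a level near 11% needs independent group effects in both arms as well as ICC 0.10. Controls take varied usual activities, and both arms appear to be recruited within the same services.
- A reader might infer that every standard error is too small. Omitting shared centre effects can make it too large.

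The layout is also uncertain. The recruitment section mentions future workshop cycles, and the Discussion reports that at least 3 CRS might lack enough people for a randomised control group, so one workshop and one control group per CRS is an assumption. Finally, the bias that the Discussion concedes, from comparing interested with uninterested users, affects the estimate itself and is probably the larger problem. That limits the weight of this point without answering it.

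**Conclusion.** The point holds as a mismatch between group delivery and individual-level sizing and analysis. With clustering in the workshop arm only and an assumed ICC of 0.01 to 0.10, the nominal 5% test runs at about 5.2% to 7.5–8% with roughly 6 per workshop, and up to 10–11% with workshops of 10. At ICC 0.01 the effect is negligible, but nothing in the article supports assuming so low a value. Power on the article's test with 128 evaluable falls from 0.815 to about 0.77 or 0.72 (ICC 0.05 or 0.10, about 6 per workshop) if ρ is near 0. It remains at or above about 0.92 throughout if ρ is 0.5. Whether power is inadequate is therefore open. The ICC, ρ and the number of workshops per CRS are all assumptions here.

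**What to change.** For outcomes analysed as sum scores, make the primary analysis a linear mixed model of the post-workshop score on baseline score and group. Include CRS as a blocking term and a workshop-level (CRS-by-group) random effect in the intervention arm, with small-sample degrees of freedom. This handles both directions of error.

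Keep a CRS and workshop identifier in the analysis file. The article lists only sociodemographic variables and an alphanumeric code assigned by CRS staff, so it is not clear that the file holds one. Because the research team is to stay unaware of group until interpretation, store it as a coded label and write the model code beforehand.

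Restate power over an ICC range such as 0.01 to 0.10, giving the assumed correlation between measurements and the workshop size. The article describes the recruitment period as past, so this corrects the stated precision and need not change the recruitment target.

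The cost is slightly wider intervals, a possibly lower stated power and one identifier to retain. No new outcome data are needed.
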